**Figure 2 F2:**
[figure not shown]
Categorization of structural interventions.

### Sample size

Sample sizes were calculated for both the primary outcomes to provide at least 80% power at the 5% significance level. Based on heat-related symptoms and illness prevalence of 28.9%^29^ and an estimated intra-cluster correlation coefficient (ICC) of 0.0122, we calculate that 11 clusters per arm (22 clusters in total) with 70–80 households per cluster are needed to detect a 30% relative difference in heat-related illnesses while allowing for a 10% attrition rate. We treat 28.9% as a conservative estimate given the longitudinal nature of the primary outcome, as cumulative incidence over the surveillance period is expected to exceed this single-timepoint prevalence. To assess quality of life changes, we estimate that with 11 clusters per arm, 60 households per cluster are required based on the variability in baseline WHOQOL-BREF scores reported,^30^ which documented an average score of 68 (18.0) to detect a difference of 4 points in quality of life score, assuming an ICC of 0.015. As the heat-related illness outcome required the larger sample size, the final enrolment target was set at 70–80 households per cluster, which also provides adequate power for the quality-of-life outcome. To assess physiological heat strain, we calculated that a sub-sample of eight adults (aged 18 years–60 years) per cluster (balanced by gender) would be required to detect a 15% change in average heart rate among those who are exposed to heat stress, assuming a baseline of 66±12 bpm,^31^ an ICC of 0.1736 and 90% power. Given the complexity of the assessment process, we anticipate a higher attrition rate in this subset and have inflated the sample size by 30% to 10 individuals.

For binary outcomes, the ICC was derived from an assumed cluster-level prevalence variation of ±10%, with the coefficient of variation (CV) estimated from this range and the ICC subsequently calculated using the relationship ICC=k² × P/(1−P), where k is the assumed between-cluster CV of the prevalence, following Pagel *et al*.^32^ For continuous outcomes, the ICC was estimated as the ratio of between-cluster variance to total variance,^33^ with total variance sourced from reference studies and a minimum between-cluster difference of ±9 units assumed. Each co-primary outcome is independently powered at 80% or above. To control the family-wise type I error rate across the two co-primary outcomes, hypotheses will be tested using a pre-specified fixed-sequence (hierarchical) procedure: heat-related illness will be tested first at the two-sided 0.05 level, and quality of life will be tested at 0.05 only if the first test is significant. As each outcome is independently powered, this procedure incurs no loss of power. Quality of life is assessed at three time points per year over 2 years; the cross-sectional calculation above is therefore conservative, as the planned repeated-measures mixed-effects analysis increases precision by combining information across visits.

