### Cluster randomisation

We will employ a constrained randomisation procedure as described by Lock, Morgan and Rubin (2012),^36^ rather than relying on a single random allocation, the randomisation process will be implemented using the Stata ‘randomise’ command, which generates multiple allocation schemes in the background and evaluates balance across prespecified baseline covariates. An allocation achieving an acceptable level of balance between study arms at the cluster level will then be selected for the trial. Geographically designed clusters will be randomly assigned by an independent statistician to either the intervention arm, receiving the Heat Adaptation Bundle (ReHAB) or the control arm. Each random allocation is evaluated for covariate balance on three pre-specified characteristics: population residential density, household structural type (single-storey vs double-storey) and roof type (permanent, semi-permanent or natural materials).

Additionally, simple randomisation would be used to select eight households for the in-depth assessment from a subset in both intervention and control groups. Within these selected households, the Kish grid method would be used to randomly select the eligible adult if more than one adult is present. If the indexed participant refuses, the next eligible adult will be considered from the same household. If all eligible adults from a household refuse to participate, then another household will be included. Male and female participants for the subset will be selected systematically.

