Individual heat exposure of a subset of participants (eight per cluster) will be measured by attaching a thermochron ibutton or Temp-U to their clothing. The participants will be instructed to always wear this logger. At the time of sleeping, they will be instructed to place the logger on their bedside.

The participants from the sub-set will be provided with Fitbit Inspire 3 devices to record physiological markers: heart rate, daily body temperature change, sleep, energy expenditure and activity. These smartwatches will be synced to the AKU server weekly and returned to the participants after charging.

Participant compliance will be monitored through spot checks and periodic review of device data. For Fitbit devices, heart rate data will be reviewed, as prolonged absence of heart rate recordings may indicate that the device was not worn. Similarly, iButton and Temp-U data will be checked periodically for implausible temperature spikes or sudden drops, which may indicate non-compliance or incorrect device use.

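### The physiological subset is ten per cluster in the sample size section but eight in selection and measurement, and the stated 30% inflation is 25% as applied

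*Protocol article*

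**What the plan says.** Three sections of the protocol article bear on the size of the physiological subset.

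- **Sample size.** The authors write "we calculated that a sub-sample of eight adults" per cluster, balanced by gender, would be needed "to detect a 15% change in average heart rate", "assuming a baseline of 66±12 bpm", "an ICC of 0.1736 and 90% power". They add that "we anticipate a higher attrition rate in this subset" and that they "have inflated the sample size by 30% to 10 individuals".
- **Cluster randomisation.** Here "simple randomisation would be used to select eight households for the in-depth assessment". One adult is then drawn from each household by Kish grid. Another adult, or another household, is taken only when those first approached refuse.
- **Data collection from subset population.** "Individual heat exposure of a subset of participants (eight per cluster) will be measured" with a clothing-mounted logger, and the subset also receives Fitbit devices.

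The figure of ten appears only in the Sample size section. The outcome schedule (Table 3) names the subset without giving a number.

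**The concern.** The sample size section ends at ten per cluster, and the sections that instruct the field team say eight. These cannot both be followed. If eight are selected, the extra recruitment meant to absorb attrition does not happen.

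The step from eight to ten is also not the 30% it is said to be, and the text does not say what rate of loss ten is meant to cover.

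The subset supplies a stated secondary objective (sleep, heart rate, activity and energy expenditure). With two targets on paper, nobody can say whether eight enrolled per cluster meets the plan or falls 20% short of it (44/220), and retention has no fixed denominator. Each subset member carries a wearable and a personal logger, so equipment needs depend on the same number, although the article states no device count.

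**Working it through.** **Inputs from the Sample size section:** 8 required and 10 after inflation; 30% inflation; 11 clusters per arm, 22 in all; a 15% change on a baseline of 66 bpm, so d = 0.15 × 66 = 9.9 bpm; SD 12; ICC 0.1736; 90% power.

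**Assumed:** two-sided 5%. The article states 5% for the primary outcomes and two-sided testing for heat-related illness, but gives neither for the subset.

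**1. The two totals**

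- Sample size section: 22 × 10 = 220.
- Selection and measurement sections: 22 × 8 = 176.
- Difference: 44 people.

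**2. The inflation**

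- As applied: 10/8 − 1 = 25%.
- As described: 8 × 1.30 = 10.4, which becomes ten only by rounding down. Rounding up gives 11.
- Largest loss at which ten still leaves eight: 1 − 8/10 = 20%.
- If 30% is a multiplier, the loss it offsets is 1 − 1/1.3 = 23.1%, and ten leaves 10/1.3 = 7.7.
- If 30% is the loss rate (an assumption), ten leaves 10 × 0.7 = 7.0 and eight leaves 8 × 0.7 = 5.6. Keeping eight needs 8/0.7 = 11.4, so 12.

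On either reading, ten leaves slightly fewer than eight.

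**3. The base figure of eight**

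Without clustering, n per arm = 2 × [12 × (1.96 + 1.2816)/9.9]² = 30.9. With design effect 1 + (m − 1) × ICC and 11 clusters per arm, the number per cluster is

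m = n(1 − ICC)/(11 − n × ICC) = 30.9 × 0.8264/(11 − 30.9 × 0.1736) ≈ 4.5.

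That is five by the normal approximation. A t reference with 20 degrees of freedom gives six. Eight is therefore not reproduced as the minimum for 90% power, but it exceeds that minimum.

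**4. Power at the numbers that might remain**

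SE = 12 × √{2[1 + (m − 1) × 0.1736]/(11m)}; power by the normal approximation = Φ(9.9/SE − 1.96). The t column uses the noncentral t with 2 × (11 − 1) = 20 degrees of freedom.

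| Completers per cluster (m) | Arises from | SE | Power, normal | Power, t |
|---|---|---|---|---|
| 8 | eight enrolled, no loss | 2.69 | 95.7% | 93.8% |
| 7 | ten enrolled, 30% lost | 2.76 | 94.8% | 92.6% |
| 5.6 | eight enrolled, 30% lost | 2.90 | 92.7% | 90.1% |

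Example for m = 8: the design effect is 1 + 7 × 0.1736 = 2.215; SE = 12 × √(2 × 2.215/88) = 2.69; 9.9/2.69 − 1.96 ≈ 1.72; Φ(1.72) ≈ 0.957.

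**The case against.** The strongest reply is that this is largely editorial. The 30% is given as the size of the inflation, not as an attrition rate, so the figures 12, 7 and 5.6 rest on a reading. Taken literally, 8 × 1.3 = 10.4 written as ten is a rounding down of 0.4 per cluster. These are subset outcomes, not co-primary ones, and 90% power survives in every case computed. All of this stands and limits the point. It does not remove the conflict between ten and eight, which needs no assumption.

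Two ways of explaining the conflict away do not work. Replacement does not supply the allowance, because the rule covers refusal at selection, whereas the inflation is for attrition. Nor can eight mean completers, because the Cluster randomisation section uses it for the number of households drawn, before any loss. That section does not itself say per cluster, but the subset data collection section does.

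A reader might infer that eight is itself a wrong sample size, because five or six would reach 90% on the stated inputs. The documents do not support that. Alpha, sidedness and the small-sample method for the subset are not given. The effect is also defined among people exposed to heat stress, and the article does not show how the calculation allowed for this. Choosing more than the minimum is conservative, not an error.

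**Conclusion.** The point holds as an inconsistency in a stated sample size, with a smaller fault in how the inflation is described.

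- **Firm, without assumptions:** ten per cluster against eight (220 against 176 over 22 clusters); an inflation of 25% where 30% is stated; ten protects eight completers only up to 20% loss.
- **Conditional on 30% being the loss rate:** ten leaves 7, eight leaves 5.6, and keeping eight would need 12.

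A reader might also infer that the subset is underpowered. That is not shown. With 5.6 to 8 completers per cluster, power is about 90% to 96%, on the stated effect, SD and ICC, 11 clusters per arm, two-sided 5%, and one mean per person with loss spread evenly over clusters. The low end, eight enrolled with 30% lost, is 90.1% by the t calculation and leaves almost no margin for heavier or uneven loss.

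The article does not show which number is intended, so neither should be presumed correct.

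**What to change.** 1. Use one enrolment number per cluster in the Sample size, Cluster randomisation and Data collection from subset population sections. The sponsor should say which is intended.
2. Correct the inflation statement: give the expected loss rate and the formula, and describe eight to ten as a 25% increase if ten is kept.
3. State the expected number of completers per cluster and the power at that number, with the alpha and sidedness used.

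Either stated number can be defended:

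- **Eight enrolled (176):** about 90% to 93% power after 30% loss. The Sample size section changes and the procedures stay as they are.
- **Ten enrolled (220):** about 93% to 95% power with seven remaining after 30% loss. The two procedural sections change to ten, and the text says that ten preserves eight completers only up to 20% loss.

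The first option costs wording only. The second means recruiting and equipping 44 more people than the procedures now provide for, but no more than the Sample size section already announces. Twelve per cluster would be needed only if the sponsor insists on eight completers at 30% loss; the stated 90% power does not require it.

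### The ±9-unit between-cluster difference given for continuous outcomes does not reproduce the stated ICCs of 0.015 (quality of life) and 0.1736 (heart rate); the figures must be reconciled

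*Protocol article*

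**What the plan says.** All the relevant statements are in the Sample size section of the protocol article.

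- Quality of life (co-primary): SD 18.0, 11 clusters per arm and 60 households per cluster, "to detect a difference of 4 points in quality of life score, assuming an ICC of 0.015". Enrolment is set at 70–80 households per cluster because heat-related illness needs more.
- Heart rate (subset): SD 12 bpm, "an ICC of 0.1736 and 90% power".
- Binary outcome: prevalence 28.9% and ICC 0.0122, derived from a ±10% variation between clusters through k²P/(1−P), where k is the between-cluster coefficient of variation.
- Continuous outcomes: the ICC is between-cluster variance over total variance, with total variance from reference studies and "a minimum between-cluster difference of ±9 units assumed".
- Power: "Each co-primary outcome is independently powered at 80% or above". The quality-of-life calculation is also called conservative because visits are repeated.

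The article does not say how 9 units were turned into a variance.

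**The concern.** One sentence gives a single numerical input for the continuous-outcome ICCs, and neither printed ICC follows from it under the conversion that reproduces the binary ICC. For heart rate the gap is modest and concerns a subset outcome. For quality of life it is a factor of about four in the ICC of a co-primary outcome. With only 11 clusters per arm, power is very sensitive to that ICC. The 60 households per cluster, the claim of at least 80% power for each co-primary outcome, and the statement that fixed-sequence testing costs no power all depend on 0.015 being the value the authors meant.

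**Working it through.** **Inputs** (Sample size section): quality of life SD 18, so total variance 324; difference 4; two-sided 0.05; 11 clusters per arm; heart rate SD 12, so total variance 144; prevalence P = 0.289.

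**1. The plan's own sample size reproduces from ICC 0.015.** Under individual randomisation, n per arm = 2 × (1.96 + 0.8416)² × 324 / 4² = 318. With k clusters per arm, households per cluster m = n(1 − ICC)/(k − n × ICC).
- k = 11: 318 × 0.985 / (11 − 4.77) = 50.3.
- k = 10 (one cluster per arm held back as a small-sample correction): 318 × 0.985 / (10 − 4.77) = 59.9.
- A t-based calculation with 20 df gives 61.

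At m = 60 the design effect is 1 + 59 × 0.015 = 1.885 and SE = √(2 × 324 × 1.885 / 660) = 1.360. Power is 83.7% (normal) or 79.9% (t, 20 df). The stated 60 is therefore consistent with 0.015.

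**2. The conversion that reproduces the binary ICC.** Taking ±10 percentage points as ±2 SD gives SD 0.05, k = 0.05/0.289 = 0.173, and ICC = 0.173² × 0.289/0.711 = 0.0122, as stated. Other conversions tried do not match: half-width/1.96 gives 0.0127, a uniform range 0.0162, half-width as the SD 0.0487, and a relative ±10% halved 0.0010.

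**3. The same conversion applied to ±9.** Between-cluster SD = 9/2 = 4.5 and variance 20.25.
- Quality of life: 20.25/324 = 0.0625 (stated 0.015).
- Heart rate: 20.25/144 = 0.141 (stated 0.1736).

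**4. What the stated ICCs imply.**
- Quality of life: √(0.015 × 324) = 2.20, about ±4.4 points.
- Heart rate: √(0.1736 × 144) = 5.00, or ±10 bpm.

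**5. Other readings of 9 for quality of life.** As a half-width: /1.96 gives 0.065, /3 gives 0.028, a uniform range gives 0.083, and 9 as the SD gives 0.25. As a full width (SD 9/4 = 2.25, variance 5.06): 5.06/324 = 0.0156, or 5.06/(324 + 5.06) = 0.0154. The full-width reading gives 5.06/144 = 0.035 for heart rate.

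**6. Consequence if ±9 points is intended for quality of life.** At ICC 0.0625, n × ICC = 318 × 0.0625 = 19.9. This exceeds 11, so no cluster size reaches 80% in the unadjusted cross-sectional calculation.
- m = 60: design effect 4.688, SE = √(648 × 4.688/660) = 2.145, power 46.2% (normal) or 42.7% (t).
- m = 80: 48.1% or 44.5%.
- Unlimited m: SE = √(2 × 20.25/11) = 1.92, power 55.0% or 51.0%.
- Difference detectable with 80% power at m = 75: SE = √(648 × 5.625/825) = 2.10, and 2.80 × 2.10 = 5.9 points (normal), or 6.2 (t).

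**7. Consequence if 9 is a full width.** At ICC 0.0154–0.0156 and m = 60–80, power is about 79–88%.

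**The case against.** A reader might infer that the trial has only about 45% power for quality of life. The documents do not support that, for three reasons.

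- The ICC stated as the design input is 0.015, and the sample size works with it. The ±2 SD conversion is inferred from the binary calculation. Continuous outcomes have their own method and citation, and that source is not shown.
- A total spread of 9 points comes close to the stated value (0.0154–0.0156). A stray ± sign would then be the whole fault for quality of life, and power would be essentially as claimed.
- The 43–48% is unadjusted. The Statistical analysis section plans adjustment for baseline outcome values where available, and the baseline survey modules include quality of life. If the cluster effect were fully stable over time, the cluster-mean correlation at m = 60 would be 20.25/(20.25 + 303.75/60) = 0.80, and adjusted power about 84–87%. With an assumed cluster autocorrelation of 0.5–0.9 it would be about 49–77%.

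All three stand against the stronger reading, but none removes the contradiction. The word minimum could accommodate ±10 for heart rate, since 10 exceeds 9. It does not accommodate ±4.4 for quality of life, which lies below that floor. Treating 9 as a minimum full width would fit both outcomes approximately, but that is not what ±9 denotes, and the heart-rate range would still be unstated. Repeated visits alone do not rescue the power claim: averaging them reduces individual noise but not a stable between-cluster component, so the 51–55% ceiling holds without baseline adjustment.

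**Conclusion.** The contradiction is real. Under the conversion that gives the binary ICC, ±9 produces neither continuous ICC, and no single value of 9, read as a half-width or as a full width, yields both 0.015 and 0.1736. For quality of life, either ±9 or 0.015 is misstated, and the article cannot settle which.

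The size depends on the answer. If 0.015 stands, the design calculation is sound (about 80–84% power at 60 households per cluster) and only the explanatory clause is wrong. If ±9 points is intended, the ICC is 0.0625 and unadjusted cross-sectional power for 4 points is about 43–48%. Adjustment could then restore 80% only with a cluster-mean baseline correlation of about 0.8: at 75 households, a correlation of 0.7 gives 71.5% and 0.8 gives 85.3% (t). The article states no such correlation. These figures assume the ±2 SD conversion, SD 18 and equal cluster sizes. The heat-related illness ICC is not in question.

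**What to change.** State, for each continuous outcome, the between-cluster range assumed, how it was converted to a variance, and why that range is plausible. Then do one of the following.

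- If 0.015 stands, replace ±9 with the range actually used: about ±4.4 to ±4.5 points for quality of life and ±10 bpm for heart rate.
- If ±9 points is intended for quality of life, restate the ICC as 0.0625, the unadjusted cross-sectional power for 4 points as about 43–48%, and the detectable difference as about 6 points. Drop the statements that this outcome is independently powered at 80% or above and that its calculation is conservative, unless a stated and justified baseline correlation (about 0.8 between cluster means) supports them.

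The cost is a recalculation and one paragraph. A stated power may become less favourable. No extra enrolment and no change to the planned tests are needed.

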### Statistical analysis

The trial has two co-primary outcomes, heat-related illness and quality of life. These outcomes will be evaluated independently to assess the effectiveness of the intervention. All statistical analyses will be conducted using STATA 18.0 (https://www.stata.com), following an intention-to-treat approach while accounting for the cluster-randomised trial design. Baseline characteristics will be analysed to assess comparability between intervention and control arms. Descriptive statistics will summarise household and participant characteristics, and any important imbalances at baseline will be adjusted for in the analysis. No interim analysis or formal stopping guidelines are planned given the low-risk nature of the intervention.

Statistical analyses will account for the cluster-randomised design by incorporating clustering through random effects or robust variance estimators, as appropriate. For outcomes measured repeatedly over time, within-participant correlation will be accommodated using repeated-measures mixed-effects models. Intervention assignment and seasonal variation will be included as fixed effects in all applicable models, while relevant baseline covariates and baseline outcome values (where available) will be adjusted for. Model assumptions, including overdispersion for count outcomes, will be assessed and alternative modelling approaches (eg, negative binomial models) will be used where appropriate. Missing data will be examined and handled using complete-case analyses or multiple imputations, depending on the extent and pattern of missingness. Sensitivity analyses will be performed to assess the robustness of findings to different assumptions regarding missing data.

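### The fixed sequence costs no power for heat-related illness only; quality of life needs both tests to succeed, and the protocol does not give its power through that gate

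*Protocol article*

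**What the plan says.** The Sample size section sizes the two co-primary outcomes separately: "Sample sizes were calculated for both the primary outcomes to provide at least 80% power at the 5% significance level". It then sets a fixed sequence. The opening step reads: "heat-related illness will be tested first at the two-sided 0.05 level". The gate for the other outcome follows in the same sentence: "quality of life will be tested at 0.05 only if the first test is significant". It describes the power as follows: "Each co-primary outcome is independently powered at 80% or above". From this it concludes: "As each outcome is independently powered, this procedure incurs no loss of power". No power is given for declaring quality of life through the sequence.

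The Statistical analysis section says of the same two outcomes: "These outcomes will be evaluated independently to assess the effectiveness of the intervention". Neither that section nor its subsection on the primary outcome analysis mentions the sequence.

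**The concern.** A fixed sequence lets each hypothesis be tested at the full 0.05, so it costs no alpha, and the first hypothesis loses no power. The second hypothesis does pay. Quality of life is declared only when heat-related illness and quality of life are both significant, and powering each test separately does not remove that condition. The conclusion therefore does not follow from its premise.

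Quality of life carries one of the two primary objectives. A reader who takes the sentence at face value will believe that the chance of a formal quality-of-life claim is at least 80%. On the stated inputs it may well be lower, and it also depends on a heat-illness effect that has nothing to do with the quality-of-life assumptions.

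**Working it through.** **Inputs, all from the Sample size section.** 11 clusters per arm; 70–80 households per cluster; 10% attrition, so 63–72 evaluable. Heat-related illness: 28.9% against 0.7 × 28.9% = 20.23%, ICC 0.0122. Quality of life: difference 4, SD 18, ICC 0.015. Two-sided 0.05. The correlation between the two test statistics is not given, so it is varied here from 0 to 0.9.

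**Step 1: reproduce the stated sizes.** With m evaluable households per cluster, the effective number per arm is 11m / (1 + (m − 1) × ICC).

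- Heat-related illness: 80% power needs m = 60.6 (normal approximation), or 60.6 / 0.9 = 67.3 enrolled. With a t reference on 20 degrees of freedom it needs 71.7, or 79.7 enrolled. These bracket the stated 70–80.
- Quality of life: the t version needs 60.5, against the stated 60. Power at 60 is 79.9% (t) or 83.7% (normal).

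The stand-alone claim of 80% or above therefore reproduces.

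**Step 2: stand-alone power at the planned size (normal approximation, unpooled variance).**

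- Heat-related illness, m = 63: effective n = 693 / 1.7564 = 394.6; SE = √[(0.289 × 0.711 + 0.2023 × 0.7977) / 394.6] = 0.0305; power = Φ(0.0867 / 0.0305 − 1.96) = 81.2%. At m = 72: effective n = 792 / 1.8662 = 424.4; power 83.9%.
- Quality of life, m = 63: effective n = 693 / 1.93 = 359.1; SE = 18 × √(2 / 359.1) = 1.343; power = Φ(4 / 1.343 − 1.96) = 84.6%. At m = 72: effective n = 792 / 2.065 = 383.5; power 86.8%.

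**Step 3: power through the gate.** This is P(both tests significant): the product of the two powers at correlation 0, and a bivariate normal probability otherwise.

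| Setting | Heat illness / quality of life alone | Corr. 0 | Corr. 0.5 | Corr. 0.9 |
|---|---|---|---|---|
| Stated floor | 80% / 80% | 64% | 69% | 75% |
| m = 63, normal | 81.2% / 84.6% | 69% | 73% | 78% |
| m = 72, normal | 83.9% / 86.8% | 73% | 76% | 81% |
| m = 63, t (20 df) | 77.2% / 80.8% | 62% | 67% | 74% |
| m = 72, t (20 df) | 80.1% / 83.3% | 67% | 71% | 77% |

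For example, 0.80 × 0.80 = 0.64 and 0.812 × 0.846 = 0.69. In every row the gated figure is below both stand-alone powers.

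**Step 4: dependence on the first effect.** If the true relative reduction in heat-related illness were 20% (assumed), its power would be 46–49% for m = 63 to 72. Quality-of-life power through the gate would then be about 39–42% at correlation 0 and 43–46% at 0.5, with the quality-of-life effect unchanged.

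**The case against.** The strongest reply is that heat-illness power is probably above the floor, so little is lost. The protocol claims at least 80%, not exactly 80%. It calls 28.9% conservative because cumulative incidence should be higher, and its Table 3 counts heat-related illness in all household members, whereas the calculation counts households. With three members per household (assumed), m = 67.5 and the ICC held at 0.0122, heat-illness power is about 95% and gated quality-of-life power about 82–83% for correlations 0 to 0.5.

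This stands as a limit on the size of the loss, but it does not make the sentence true: 82–83% is still below the stand-alone 86% at that size. The gain is also uncertain. At an assumed incidence of 40%, the protocol's own relationship ICC = k² × P/(1 − P), with k² = 0.0122 × 0.711/0.289 = 0.030, raises the ICC to 0.020. Heat-illness power is then 88.5–90.2% for m = 63 to 72, and gated quality-of-life power at correlation 0 is 0.885 × 0.846 = 75% to 0.902 × 0.868 = 78%.

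The protocol also calls the quality-of-life calculation conservative because of repeated visits. That raises stand-alone power only; the heat-illness power remains the ceiling.

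The authors may have meant that the sequence avoids splitting alpha. That is correct, but the sentence as written says more.

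Finally, the wording in the Statistical analysis section might be read as permitting a quality-of-life claim after a failed first test. Two ungated tests at 0.05 would give a family-wise error of 1 − 0.95² = 9.75% if independent. The documents do not support that as a finding. Independent evaluation reads naturally as separate models, the same adverb is applied to power right beside the gate, and the gate is explicit and pre-specified. What remains is a wording risk.

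**Conclusion.** The statement that the procedure loses no power is wrong for quality of life and right for heat-related illness. The direction needs no assumption about correlation: gated power cannot exceed the heat-illness power. The size does. It is 64–75% at the 80% floor, or about 69–81% at the planned size under the normal approximation, for correlations from 0 to 0.9.

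A reader might infer that quality-of-life power is definitely below 80%. The documents do not support that: about 80% is reached at correlation 0.9, and 82–83% if heat-illness power is near 95%. Nor is the claim of 80% or above itself an error, since it describes stand-alone power and reproduces. The alpha allocation, test order and sample size arithmetic are not affected.

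**What to change.** In the Sample size section:

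- limit the sentence on power loss to the first hypothesis;
- say that 80% or above is the stand-alone power of each test;
- report quality-of-life power through the gate over a stated range of correlations and heat-illness powers, noting that heat-illness power is its upper limit. If the conservative margin is relied on, put a figure on it.

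In the Statistical analysis section, say that the two outcomes are modelled separately but tested in the fixed sequence set out under Sample size.

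The cost is a few sentences and a short calculation. Design, data collection and recruitment need not change. The price is a less favourable power statement for the second co-primary outcome.
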